
**Figure 2 F2:**
[figure not shown]
Algorithms for different levels of the warning system and corresponding treatment recommendations.

### Outcome measurements

2.4

The primary outcome is change in the clinical classification of COVID-19 patients, including postintervention and treatment. The clinical experts will perform disease severity and final clinical classification assessment according to predetermined criteria.

Secondary outcomes include the proportion of patients with different disease severity types; critical deterioration events of patients during treatment, including total incidences and classification of each type of event; patients with unplanned transfers to ICU and requiring critical care interventions (mechanical ventilation, noninvasive ventilation, inotropes, and/or other organ-supported therapies) during treatment; time intervals from patient warning information received to implementation of clinical interventions; the severity of illness at unplanned transfer to ICU; hospital mortality; length of ICU and hospital stay; workload of physicians and nurses during study period; risks of exposure to potential COVID-19 patients.

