**Method::**

The research is designed as a prospective cohort study, to verify a dynamic and interactive evaluation system; it includes patient self-reporting, active monitoring, early alarming and treatment recommendations. Adult patients diagnosed with COVID-19 will be recruited from Sept 2020 to Aug 2021 at a tertiary contagious hospital. Patients with life expectancy <48 hours, pregnant or lactating, in immunosuppression states or end-stage diseases will be excluded. The intervention is implementation of EWRRS to detect early signs of clinical deterioration of COVID-19 patients, to provide timely and efficient treatment suggestions by the system. EWRRS can determine the classification and interactive evaluation of patient information; the determination is based on the application of 3 different scenario modules, separately driven by patients, nurses, and physicians. The primary outcome is change in disease severity category after treatment. Secondary outcomes include the proportion of patients with different disease severity types; critical deterioration events; patients who had unplanned transfers to an intensive care unit (ICU) and required critical care interventions; intervals from warning to implementation of clinical interventions; hospital mortality; length of ICU and hospital stay; workload of medical staff and risks of exposure to COVID-19.

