### Study design and aims

2.1

This is a stepped-wedge prospective mixed methods study exploring the feasibility of EWRRS, which is an interactive, multimodal screening program to support the early identification of potential patients who may progress from mild or moderate to severe or critical illness. The detailed study aims:

1.To improve the detection of early signs of clinical deterioration of COVID-19 patients and provide real-time data to the entire clinical team, thus improving team situation awareness of patient deterioration.2.To provide timely and efficient treatment suggestions for COVID-19 patients through the rapid response system, thereby promoting active management of deterioration, stabilizing patient conditions early and avoiding the progression of deterioration to a more serious degree.3.To reduce the workload and risks of occupational exposure of medical personnel during the epidemic through interactive, multimodular processes.4.To identify the COVID-19 progression patterns and characteristics through big data analysis, thus providing an example of EWRRS for future outbreaks of public health events. Moreover, such a system can potentially be extended for use as a grading EWRRS, to respond to deteriorating patients outside of an ICU setting.

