### Study population and setting

2.2

Patients are eligible for this study if they were diagnosed with COVID-19 according to the New Coronavirus Pneumonia Prevention and Control Program (7th edition), published by the National Health Commission of China.^[5]^ Inclusion criteria comprise the following: adult patients (18 years or older) with clear epidemiological history; fever and/or respiratory symptoms; normal or decreased white blood cell count and/or lymphocyte count; high degree of suspected imaging characteristics of novel coronavirus pneumonia; positive results of SARS-CoV-2 nucleic acid detection and serum-specific antibodies; ability to provide a signed informed consent form. Patients were excluded if known life expectancy was less than 48 hours, pregnant or lactating, diagnosed with end-stage diseases, or in immunosuppression states.

Clinical Classification of the COVID-19 patients is according to their disease severity upon admission: *Mild cases*: The clinical symptoms are mild and no pneumonia manifestations can be found in imaging. *Moderate cases*: Patients have symptoms such as fever and respiratory tract symptoms, etc. and pneumonia manifestations can be seen in imaging. *Severe cases*: Adults who meet any of the following criteria: respiratory rate ≥30 breaths /min; oxygen saturation ≤ 93% at a rest state; arterial partial pressure of oxygen (PaO_2_)/oxygen concentration (FiO_2_) ≤ 300 mm Hg; patients with > 50% lesion progression within 24 to 48 hours in lung imaging. *Critical cases*: Adults who meet any of the following criteria: occurrence of respiratory failure requiring mechanical ventilation; presence of shock; other organ failure that requires monitoring and treatment in the ICU.

*Hospital discharge criteria*: normal body temperature for more than 3 days; significantly improved respiratory symptoms, that is, no oxygen supplementation requirement, stable and normal vital signs for longer than 1 day; lung imaging showing obvious absorption and resolution of acute infiltrates; negative results of the nucleic acid test for SARS-CoV-2 two times consecutively, with at least a 1-day interval between tests.

Patient recruitment duration will last for a year, from September 2020 to August 2021. During the study period, patients diagnosed with COVID-19 will be directly admitted or transferred to Beijing Ditan Hospital, which is the government designated COVID-19 hospital.

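### The primary outcome has no time point and no place for death; read at end of stay, as its wording suggests, it largely misses progression followed by recovery

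*Protocol article*

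**What the plan says.** The abstract (Method) states: "The primary outcome is change in disease severity category after treatment". Section 2.4 words it differently: "The primary outcome is change in the clinical classification of COVID-19 patients, including postintervention and treatment". It continues: "The clinical experts will perform disease severity and final clinical classification assessment according to predetermined criteria". None of these sentences names a day or an event for the second classification.

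The starting point is clear. Section 2.2 says: "Clinical Classification of the COVID-19 patients is according to their disease severity upon admission". It defines four classes (mild, moderate, severe, critical), and death is not among them. The severe class includes "oxygen saturation ≤ 93% at a rest state", a respiratory rate of 30/min or more, PaO2/FiO2 of 300 mm Hg or less, and more than 50% lesion progression. The critical class is respiratory failure needing ventilation, shock, or organ failure needing the ICU.

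The same section sets the discharge criteria. Besides temperature, resolving imaging and two negative tests, they require "no oxygen supplementation requirement, stable and normal vital signs for longer than 1 day".

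Aim 2 in section 2.1 includes "avoiding the progression of deterioration to a more serious degree".

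**The concern.** The event that the system is meant to prevent happens during the stay. An outcome that compares admission with the end of the stay sees only the two ends. If discharge itself requires a state that excludes the severe and critical classes, the second reading is nearly constant among survivors, and the change carries little beyond the admission class.

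At stake is the main result. A system that halved progression and one that doubled it could give almost the same primary outcome among survivors. A difference that did appear among survivors would mainly show that one group contained more patients who were severe at admission. That matters in a stepped-wedge comparison (section 2.1), where the groups come from different calendar periods.

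**Working it through.** The article states no sample size, power or event rate, so there is no figure to reproduce. The main check sets the discharge criteria against the class definitions; the arithmetic after it is illustrative.

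**Step 1. Can a patient who meets the discharge criteria be severe or critical (both section 2.2)?**

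| Severe or critical criterion | Discharge requirement that bears on it | Compatible? |
|---|---|---|
| Respiratory rate ≥30/min | Normal vital signs | No |
| Resting SpO2 ≤93% | Normal vital signs, no oxygen need | No |
| >50% lesion progression in 24 to 48 h | Resolving infiltrates | No |
| PaO2/FiO2 ≤300 mm Hg | Not named; on room air 300 × 0.21 = 63, so PaO2 ≤63 mm Hg | Hardly, with normal saturation off oxygen |
| Mechanical ventilation | No oxygen need | No |
| Shock | Normal vital signs | No |
| Organ failure needing ICU | Not named | Not in practice |

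Five of the seven are excluded by the stated criteria and two by clinical inference. Practically every discharged survivor is therefore non-severe.

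**Step 2. What change does a survivor then score?** Section 2.3 groups patients as mild/moderate, severe and critical.

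| Admission class | Course in hospital | Class at discharge | Change |
|---|---|---|---|
| Mild/moderate | Never progresses | Mild/moderate | None |
| Mild/moderate | Becomes critical, recovers | Mild/moderate | None |
| Severe | Recovers directly | Mild/moderate | Improved |
| Severe | Becomes critical, recovers | Mild/moderate | Improved |
| Critical | Recovers | Mild/moderate | Improved |

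The proportion improved among survivors thus equals the proportion of survivors who were severe or critical at admission. The proportion worsened is practically 0 in either group. Only deaths could separate the groups, and the scale does not rank them.

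**Step 3. How much could this cost? (Illustration.)**

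Assumed inputs:
- All patients are mild/moderate at admission.
- Progression to severe or critical is 30% v 15%.
- Patients are independent, with equal groups and no stepped-wedge effects.
- The test is Pearson χ² (named in section 2.6), two-sided at 0.05. The section gives the 0.05 level but not the sidedness.

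Mortality among progressors is taken as 22% to 62%, the range that the Introduction gives for severe cases.

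Worsened, if only deaths count = progression × mortality:
- at 22%: 0.30 × 0.22 = 6.6% v 0.15 × 0.22 = 3.3%
- at 62%: 0.30 × 0.62 = 18.6% v 0.15 × 0.62 = 9.3%

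Exact power = Σ over all pairs (x, y) with χ² > 3.84 of Bin(x; n, p₁) × Bin(y; n, p₂):

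| Definition of worsening | Rates | n = 100 per group | n = 150 | n = 200 |
|---|---|---|---|---|
| Worst class reached | 30% v 15% | 0.73 | 0.88 | 0.95 |
| Deaths only, mortality 62% | 18.6% v 9.3% | 0.48 | 0.65 | 0.78 |
| Deaths only, mortality 22% | 6.6% v 3.3% | 0.17 | 0.26 | 0.33 |
| Death has no class | 0 v 0 | no contrast | no contrast | no contrast |

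**The case against.** The strongest objection is that the article never ties the final classification to discharge. The wording in section 2.4 mentions the period after intervention, and both the Introduction and section 2.3 describe reclassification during treatment. The final class could also mean the one adjudicated by experts, as opposed to the system's own, and not the last in time. This stands as far as it goes: a reader might infer that the plan fixes the outcome at discharge, and the documents do not say so. It does not rescue the outcome. If the end-of-stay reading is wrong, the primary outcome has no defined time point at all, and the same repair is needed.

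Three further inferences go too far.
- **That every survivor is non-severe by rule.** The discharge criteria do not name PaO2/FiO2 or organ failure, so for those two criteria the exclusion is near-certain but inferred.
- **That any patient who becomes critical and recovers counts as unchanged.** This holds only for patients admitted mild/moderate with those classes merged. With four classes, a patient admitted mild who leaves with residual pneumonia on imaging could score one step worse. That step would not distinguish a critical course from a moderate one.
- **That the primary outcome cannot show any benefit.** Deaths could still show one if ranked, and at the upper mortality figure the power is reduced but not negligible.

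It is also true that the secondary outcomes in section 2.4 record critical deterioration events, unplanned ICU transfers and hospital mortality. Aim 2 is therefore measured, but not by the outcome on which the main conclusion rests.

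**Conclusion.** The point holds in a bounded form. As written, the primary outcome has no time point and gives death no place on the scale. On its most natural reading, the end of the stay, it is largely insensitive to progression followed by recovery, and differences among survivors mainly reflect admission case mix.

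The logical part rests only on section 2.2 and, for the merging of mild and moderate, on section 2.3. The size is illustrative: under the assumptions listed, power at 100 per group falls from 73% to between 17% and 48% if deaths are ranked, and there is no contrast if they are not. The progression rates and group sizes are assumed, and applying the severe-case mortality range to progressors is a further assumption. Because this is the primary outcome, it should be settled before any data are analysed.

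**What to change.** Define the primary outcome in section 2.4, and identically in the abstract, as the worst section 2.2 class reached between enrolment and discharge relative to the admission class, with death as the worst category. An alternative is the class on one fixed day after admission for every patient, in hospital or discharged, again with death ranked worst. State whether mild and moderate are merged. Keep the end-of-treatment class as descriptive, and give the secondary outcome on the proportions in each severity type the same time rule.

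State also that the outcome uses the section 2.2 definitions as assessed by the experts. The system's own reassessment as severe in section 2.3 uses other thresholds (for example a respiratory rate of 25/min on oxygen, against 30/min in section 2.2).

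The cost is an amendment to the outcome wording. Section 2.5 already provides for vital signs, laboratory results, imaging and complications to be recorded throughout the stay, so the worst class needs no new variables. The sponsor should confirm that the same recording covers patients in the period before the system is introduced. The fixed-day alternative would also need a way to classify patients already discharged by that day.

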### Data collection and management

2.5

After admission, the system will record the patient demographic characteristics, age, gender, and past history. Signs and symptoms, physical examination results, laboratory tests, and imaging examination will be also recorded as baseline data. During the research period, the system will dynamically record all self-report and laboratory test results of the patient throughout the process. These specific parameters include signs and symptoms: dry cough, persistent chest pain, palpitation, myalgia, shortness of breath, dyspnea, etc.; vital signs: body temperature, heart rate, respiratory rate, SpO_2_, blood pressure; laboratory tests: white blood cell count, lymphocyte count, platelet count, C-reactive protein (CRP), transaminase (AST, ALT), bilirubin, creatinine, lactate dehydrogenase, troponin, D-dimer, blood gases, etc.; diagnostic radiology of the lungs: initial and follow-up imaging features of chest X-rays, chest computed tomography scans, and evaluation of dynamic imaging findings throughout the course of the disease; complications, such as shock, cardiovascular events, renal failure, etc. All the alarming information and levels that trigger EWRRS will also be completely recorded.

The data for all patients participating in the study will be securely stored in the EWRRS and exported to a specially designed database. It will be ensured that data is collected during the entire 24 hours and on all days of the week during the study.

### Trial management

2.7

#### Coordination centers

2.7.1

The present research involved a collaboration of the Department of Critical Care Medicine, Beijing Tsinghua Changgung Hospital, and the Department of Electronic Engineering and Institute for Precision Medicine, Tsinghua University. Team members included clinical experts, statisticians and data analysts, and big data engineers. They were responsible for clinical research methodology and addressing key problems in the implementation of research.

#### Quality control

2.7.2

Sites and researchers were monitored and inspected regularly by the Hospital's Clinical Research Supervision Committee, following the standard protocol throughout the study process.

### Ethics and dissemination

2.8

Study patients or their authorized surrogates received sufficient explanation and time to sign the informed consent form before the trial. Researchers ensured that the study was conducted in accordance with the principles of the Declaration of Helsinki and the clinical trial quality management regulations in China. The study protocol has been approved by the Ethics Committee of Beijing Tsinghua Changgung Hospital (20262-0-01).

## Discussion

3

With more and more patients affected, the global COVID-19 pandemic has become a significant public health emergency. The whole world now is fighting this pandemic, building mobile cabin hospitals to isolate patients, conducting intensive clinical investigation and research studies on confirmed cases. We must overcome staffing shortages due to the need to care for more patients, healthcare personnel exposures, and illness. The data processing and evaluation system is built to collect and evaluate clinical signs and symptoms, point-of-care testing and center lab test results and their progressive dynamic changes. It will assist clinicians in filtering high-risk patients among all isolated patients.

The 2019 novel coronavirus infection is an illness mainly targeting the respiratory tract. The initial symptoms might appear nonspecifically and can go unnoticed. More serious cases might present difficulty breathing and severe hypoxemia around 7 to 10 days after exposure to the coronavirus; they will progress quickly, and eventually require mechanical ventilation. The mortality of these severe patients can be as high as 88%.^[5]^ Some might only present shortness of breath or chest distress, described by low oxygen level exhibited without dyspnea, termed as silent hypoxemia. For dynamic monitoring, it is therefore essential to identify these potentially severe cases actively.

Attentive patients are observant of illness progression. This is the foundation for the success of self-reporting of signs and symptoms, with active participation in the process of care. Previously, we created a probability and severity risk assessment matrix based on clinical presentations and auxiliary examinations, to estimate the severity of ICU patients, the risk of thrombosis, and the readmission rate for heart failure patients, etc.^[6,7]^ Here as well, the identification of a high-risk group at an early stage will bring about timely intervention, thereby reducing the possibility of medical error and hospital burden.

Besides respiratory symptoms, other factors—shortness of breath, advanced age (age 75 or older), existing cardiovascular disease, diabetes mellitus, and other underlying diseases—will influence the prognosis of the novel coronavirus pneumonia.^[8]^ Similar to severe acute respiratory syndrome (SARS) and Avian Influenza, other factors have been linked to negative clinical outcomes for these patients: continuously decreasing lymphocyte count; progressively increasing inflammatory cytokines (such as interleukin, IL-6), C-reactive protein (CRP), lactate, lactate dehydrogenase.^[9,10]^ Many clinical observation studies reported coagulopathy, reduced platelet count, and elevated D-dimer among these patients. Among 1099 COVID-19 cases, a higher percentage of severe/critical cases presented low platelet count (≤150 × 10^9^ /L) than in mild/moderate cases (57.7% vs 31.6%);^[11]^ there was a significantly higher number of patients with D-dimer ≥0.5 mg/L in severe/critical cases (59.6% vs. 43.2%). These observations suggest a close relationship between coagulopathy and the severity and prognosis of this disease. Other concomitant symptoms and injuries manifested as abnormal liver function—such as increased troponin and bilirubin—and abnormal EKG presentations.^[12–14]^ The data processing and evaluation system will include all the clinical indices mentioned above; thereafter, it will set up different warning levels, to assist clinicians in assessing the severity and need to intervene. This system will advise different levels of monitoring and intervention, to monitor high-risk patients and provide treatment solutions. The result should be a significant improvement in early warning efficiency. At the same time, the system will harvest a database for an early predicting system, by incorporating the epidemiological characteristics.

The EWRRS will be significant in several respects: It provides an example of an early identification, warning, and response system for future outbreaks of public health events. It can be converted to a regular early warning system for hospital patients with emergency events in out of ICU. It helps to identify the disease (COVID-19) progression patterns and characteristic through big data analysis.
